##### Three-week adaptive period

Twice a week for 3 weeks, participants will visit the HAP Lab to learn proper techniques and familiarize themselves with HIFT exercises. Week 1 will consist of a movement screening to assess the participant’s capabilities of multi-planar, functional movements (squat, hinge, lunge, push, pull, press, and rotation) [74, 75]. Corrections and modifications will be advised to participants, then movements will be trained to ensure proper, safe exercise. If proper movement is not attained within week 1, this familiarization will be extended until satisfaction before progression. Week 2 will consist of learning a structured HIFT routine using minimal load at half of phase 1 volume (see Fig. 1). Week 3 will consist of HIFT rehearsal bouts at ¾ of phase 1 volume (see Fig. 1). Load or resistance will be added to the exercise on an individual basis, aiming for a target perceived effort of ≥ 7 on the Borg Session RPE CR10 Scale (sRPE) [76–79]. Examples of load or resistance are bodyweight, suspension bands, medicine balls, kettlebells, dumbbells, elastic bands, and stability balls. Additionally, participants will be familiarized with the aerobic intensity target (HR ± 5 beats of second ventilatory threshold (VT2)) for each set within the HIFT session. To quantify these intensity targets, HR and sRPE will be measured immediately after each set. Participants will be familiarized with this data collection procedure and intensity target during week 3 [79]. Participants will then be randomized and scheduled for their 12 weeks of training based on their allocated dose (HIFT1, HIFT2, or HIFT3).

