#### Participant timeline {13}

Upon recruitment, participants will meet with the primary investigator and provide informed consent and health history. Next participants will be screened for the inclusion criteria at the HAP Lab at WCU. During the screening visit, participants’ height, weight, waist circumference, abdominal height, resting HR, resting BP, and resting SpO_2_ will be measured. Additionally, participants will be measured for a fasted basic blood lipid and glucose panel. Next, participants will complete a physical activity and diet questionnaire (Full Block Questionnaire, NutritionQuest, 2014) [70, 71], and all included participants will be asked to maintain their self-reported diet throughout the entire study.

Participants will begin the study with a baseline GXT immediately after the initial screening. Next, baseline metabolic testing in the HAP Lab and GVH will take place 48–72 h after. This visit will consist of a 12-h overnight fast, baseline endothelial function testing at the HAP Lab, then metabolic marker bloodwork and body composition testing via DEXA at GVH. Additionally, participants will complete the IFIS to assess self-reported fitness [85, 86]. During the following 3 weeks, participants will visit the HAP Lab twice a week for exercise familiarization and adaptation. Participants will then be randomized into 1 of 3 exercise dose groups (HIFT1, 1 session per week; HIFT2, 2 sessions per week; HIFT3, 3 sessions per week) and be scheduled for their exercise sessions for the following 12 weeks. The 12 weeks of supervised training will consist of three 4-week phases, where intensity and duration of exercise are progressed each phase. After the last exercise session, participants will be scheduled for two post-testing visits. The first visit will consist of a 12-h overnight fast, endothelial function testing, PACES and exercise intention questionnaires, and IFIS questionnaire at the HAP Lab, then metabolic marker bloodwork and body composition testing via DEXA at GVH. This visit will be scheduled no sooner than 48–72 h after the final exercise session to ensure acute lipid or glucose responses are not influenced [14, 94–96]. The second visit, 24–48 h later, will consist of the repeated GXT on a treadmill from baseline testing. See Fig. 2 for the schematic illustration of research design and Table 3 for the schedule of the study period.

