##### Endothelial function

Endothelial function will be assessed at baseline and 48–72 h after the last exercise bout of the intervention. Fasted, endothelial-dependent vasodilation of the non-dominant arm will be measured using venous occlusion strain gauge plethysmography (EC6 Strain Gauge Plethysmography System & Rapid Cuff Inflation System, Hokanson Inc., Bellevue, WA). To begin, forearm volume will be measured by the water displacement method. Then, the arm will be elevated to the level of their heart, a pneumatic cuff will be placed around the wrist and upper arm, and a strain gauge will be fixed around their lower arm. Once all measuring devices are attached and ready, the contralateral arm will be used to measure HR and BP until stable resting values are obtained (after 15 min of supine quiet rest). Next, basal blood flow will be measured for 5 min. The wrist cuff will be inflated to 220 mmHg, and the upper arm cuff will cycle between 50 and 0 mmHg every 8 and 7 s for the entire 5 min. Then, the brachial artery will be occluded for 5 min at a pressure of 220 mmHg. At the 4-min mark of the occlusion period, the wrist cuff will be inflated to 220 mmHg again. At the end of the occlusion period, the upper arm cuff will be deflated to assess reactive hyperemia for 5 min. Peak forearm blood flow and 60-s hyperemia blood flow will be quantified.

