##### Graded exercise test

Baseline and post-training cardiorespiratory fitness will be measured via a graded exercise test (GXT) on a power treadmill (CT850, Spirit Fitness, Jonesboro, AR) in the HAP Lab. Participants will be instructed on the rate of perceived exertion scale (RPE) and walking protocol, outfitted with a HR monitor (Polar F1, Polar USA, Warminster, PA), connected to a metabolic cart (Oxycon Mobile, CareFusion Respiratory Care, Yorba Linda, CA) and positioned on the treadmill. The GXT will begin with a 5-min warm-up at a self-selected pace, gradually reaching the pace they will maintain throughout the test. A modified Balke and Ware protocol will be used where participants will maintain their constant speed and incline will be increased by 1% each minute until volitional exhaustion [87]. Breath-by-breath gas exchange and continuous HR data will be collected and averaged every 15 s. RPE will be measured in the last 10 s of each minute. Participants will continue until volitional exhaustion. The first and second ventilatory thresholds (VT) will be identified and calculated as the point in which the plotted ventilation rate makes an a-linear increase. Maximal HR, VO_2_, and workload will be recorded. Participants will rest passively for 20 min after the completion of the GXT, then perform a verification trial to confirm VO_2max_ [88–90]. For the verification trial, participants will walk on the treadmill at a workload of 105% of their maximal workload during the GXT (last fully completed stage) until volitional exhaustion. If the VO_2max_ of the verification bout and GXT are within ± 3%, true VO_2max_ will be considered achieved [88, 90]. If participants are unable to reach VO_2max_, they will be asked to repeat the trial after a 24-h rest.

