#### Adverse event and reporting and harms {22}

An adverse event is defined as a medical condition occurring between the time of consent and the last trial visit that results in the inability to participate in the intervention. A serious adverse event is defined as any untoward medical occurrence that results in an immediately life-threatening condition, severe or permanent disability, prolonged hospitalization, or significant hazard as determined by the DSMB. Any adverse event or serious adverse event between the time of participant consent and the last trial visit will be recorded on the WCU HAP Lab Incident Report Form at the time of the event. If the adverse event occurs after the time of consent but before receiving the intervention, the event will be recorded as not related to the study. If the event occurs between the first and last intervention visit, the event will be reported to the DSMB. In the case of a serious adverse event, the event will be reported to the Institutional Review Board (IRB) at Western Colorado University and Ethics Committee at Auckland University of Technology. Investigators and DSMB will determine the relatedness of an event to the study intervention. Adverse events deemed related to the study will be reported in the results of the study.

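### The protocol records every adverse event between consent and the intervention as unrelated to the study, although its own maximal exercise tests fall in that window

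*Protocol article*

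**What the plan says.** The section on adverse events and harms (item 22) defines an adverse event as a medical condition, arising from consent to the last trial visit, that leaves the person unable to take part in the intervention. It then fixes the causal verdict for one part of that period. If the event "occurs after the time of consent but before receiving the intervention, the event will be recorded as not related to the study". No exception follows.

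The same section asks the investigators and the data and safety monitoring board (DSMB) to judge relatedness, but only to the study intervention. It sends events to the DSMB when they occur from the first to the last intervention visit. On publication it states: "Adverse events deemed related to the study will be reported in the results of the study".

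The participant timeline (item 13) shows what lies between consent and training. Consent comes first: "Upon recruitment, participants will meet with the primary investigator and provide informed consent and health history". After screening, "Participants will begin the study with a baseline GXT immediately after the initial screening". Endothelial testing, blood draw and DEXA follow 48–72 h later, then three weeks of familiarization at two days per week, then randomization, then the 12 weeks of training.

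**The concern.** The tests in this window are done only because the person joined the trial, and some of them are strenuous. The participants are inactive adults aged 35 to 65 with at least three metabolic syndrome risk factors. Someone injured on the treadmill at baseline, badly enough to be unable to train, would have been harmed by a study procedure and yet recorded as having an event unrelated to the study.

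What is at stake is the harms record. The publication commitment covers events deemed related to the study, so an event labelled unrelated in advance falls outside it. The protocol hopes to inform exercise guidelines for people with metabolic syndrome, and readers of the results would want to know what happened when untrained participants first met maximal effort.

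**Working it through.** The protocol gives no figure on this point to reproduce. The check sets the order of procedures against the rule.

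**Baseline tests**

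- The GXT section says "incline will be increased by 1% each minute until volitional exhaustion". After 20 minutes of rest there is a second bout: "participants will walk on the treadmill at a workload of 105% of their maximal workload during the GXT". A repeat after 24 h is possible if maximal oxygen consumption is not confirmed.
- The endothelial function section says "Then, the brachial artery will be occluded for 5 min at a pressure of 220 mmHg".
- Blood draw and DEXA take place at the same baseline visit.

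All of these come after consent and before training, so on any reading of the word intervention they fall under the automatic label.

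**Run-in**

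The familiarization gives 3 weeks × 2 days = 6 sessions per person, more if week 1 is extended. It aims for a perceived effort of at least 7 on the Borg CR10 scale. On its last stage the plan says "Week 3 will consist of HIFT rehearsal bouts at ¾ of phase 1 volume". It precedes randomization, which suggests it is not the allocated intervention. But it is described under the heading for the intervention description (item 11a), which suggests it is. The document does not settle which side of the cut-off it lies on.

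**Could another provision correct the label?**

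- The relatedness judgement is tied to the study intervention. An event before the intervention cannot be related to it, so that judgement never reaches harm from a baseline procedure.
- Item 22 limits DSMB reporting to the span between intervention visits. The sections on the monitoring committee (item 21a) and on auditing (item 23) bring the DSMB in for an adverse event without a time limit. These passages do not agree.

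**Exposure inside the window** (counts of procedures, not of events)

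- Maximal bouts, assuming 60 people tested at both time points, two bouts each time, no repeats: baseline 60 × 2 = 120; total 60 × 4 = 240; share 120/240 = 50%.
- If 66 start (22 per group, as the sample size section also says) and 60 finish: 66 × 2 = 132 at baseline, 60 × 2 = 120 at the end, 132/252 = 52%.
- Supervised sessions, if the run-in is not intervention: 60 × 6 = 360. Training adds 20 × (12 + 24 + 36) = 1,440. Share 360/1,800 = 20%. If the run-in is intervention, the share is 0%.

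**The case against.** Several points on the other side are sound and limit the finding.

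- **Events are not lost.** Every adverse or serious adverse event from consent to last visit goes on the incident report form. Serious ones go to the institutional review board and the Ethics Committee with no limit by time or relatedness. The steering committee monitors safety throughout. A reader might infer that a cardiac event in the baseline test would escape oversight; the document does not support that.
- **The rule may not reach serious events.** Item 22 defines the two classes separately and names both where it means both, while the challenged sentence names only adverse events. It does not exempt serious ones either, so this is ambiguous.
- **Publication is not expressly restricted.** A reader might infer that unrelated events are barred from the results. The text commits to reporting related events and does not say that only those will appear. Omission is likely, but it is not a stated rule.
- **The trial's comparison is untouched.** These events precede randomization, so they cannot bias the contrast in ApoB between dose groups.
- **The session share is weak.** The 20% depends on the undefined status of the run-in. It also counts week 1 technique work and week 2 minimal-load sessions as equal to full training.
- **Few occurrences may qualify**, since the definition of an adverse event is narrow.

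None of this rescues the sentence itself. Recording an event does not correct its causal label, and no other provision assesses harm from baseline procedures.

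**Conclusion.** The concern holds in a limited form. Causality is decided by timing alone in a period that contains study-only procedures, some of them maximal. Followed as written, the rule gives a false label to any qualifying event that those procedures cause, and takes that event out of the plan's reporting commitment. For the baseline tests this is certain from the text. For the run-in it depends on what counts as the start of the intervention, which the protocol leaves open. The same gap blurs the DSMB reporting window, which begins at the first intervention visit.

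About half of the planned maximal bouts lie in the window, on the participant numbers assumed above. That describes exposure only; without an event rate, the number of misclassified events cannot be estimated. The damage is to the classification and completeness of published harms, not to efficacy, power or the dose-response conclusion. The point therefore should be fixed, but does not call the trial's main result into question.

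**What to change.** Amend item 22 as follows.

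1. Delete the sentence that records events before the intervention as unrelated.
2. Assess every event from consent to the last trial visit case by case, for relatedness to study procedures (screening, GXT and verification bout, plethysmography, blood draw, DEXA, run-in) as well as to the training.
3. Report in the results the events judged related to either, including those in people who were never randomized.
4. State whether the run-in counts as intervention.
5. Reconcile the DSMB reporting window, and the wording that ties relatedness to the study intervention, with items 21a and 23. State whether the relatedness rules cover serious events too.

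The cost is one short amendment and a few more relatedness assessments. No dose, schedule, sample size or analysis changes.

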#### Frequency and plans of auditing trial conduct {23}

Trial conduct will be audited every 5–6 weeks at the TSM meeting. In the case of an adverse event, the DSMB will audit the trial conduct and advise continuation and modification.

#### Plans for communicating important protocol amendments to relevant parties {25}

Any modifications to the protocol which may impact the conduct of the study and the potential benefit of the participants or may affect participant safety, including changes of study objectives, study design, participant population, sample sizes, study procedures, or significant administrative aspects will require a formal amendment to the protocol. Such amendment will be agreed upon by the principal investigators and approved by the Ethics Committee/Institutional Review Board of WCU and AUT prior to implementation.

Administrative changes of the protocol that are minor corrections and/or clarifications that have no effect on the way the study is to be conducted will be agreed upon by the principal investigators and documented in a memorandum.

#### Dissemination plan {31a}

Approximately four papers will be submitted for journal publication from the trial results. One to two abstracts will be presented at the American College of Sports Medicine annual conference. Additionally, all participants will be informed of the trial results in a personal letter from the principal investigator.

## Discussion

Approximately 1 in 3 people in the USA suffer from MetS [7]. This statistic has increased significantly in the past decades and is projected to continue in an upward trend [7]. Similar prevalence and increasing rates have been found across the globe [101]. A plethora of evidence exists demonstrating that physical activity and exercise reduce the risk factors of MetS [4, 8–10], and therefore, exercise recommendations have been published internationally [8, 22]. Despite this evidence, only 1 in 4 adults in the world and less than 25% of adults in the USA meet these recommendations [22, 51], claiming the perceived barriers of “lack of time” and “lack of enjoyment” in the prescribed exercise recommendations [52–54]. HIFT is a time-efficient modality of exercise that has been shown to elicit enjoyment and adherence [55]; improve oxygen capacity, insulin resistance, and muscular strength [58], as well as the MetS *z*-score [59] in at-risk populations; and improve cardiorespiratory fitness [60, 61], muscular strength, and power [62], as well as waist circumference and agility [61] in healthy populations. This study aims to continue the investigation of HIFT as it seems to combat the barriers to regular exercise and improve cardiometabolic risk factors.

Researchers of this modality have used several terms to define it (e.g., HIIT-type, high-intensity circuit resistance training, multimodal high-intensity training, high-intensity interval neuromuscular training, functional high-intensity training); all terms trying to describe a modality of exercise that combines aerobic and functional resistance training performed in an interval fashion and completed in a time-efficient manner. These modalities seem to be trying to achieve a similar thing, to combat the barriers to exercise and optimize the physiological responses to achieve comprehensive health and fitness benefits. Recently, a paper was published synthesizing this initiative and modality into common terminology, high-intensity functional training (HIFT), in order to formalize a definition for better access and comparison of future studies [57]. HIFT emphasizes functional, multi-joint movements via both aerobic and muscle-strengthening exercises [57]. These exercises (e.g., squats, push-ups, pull-ups, deadlifts, weighted carry) are designed to improve the pattern of movement for activities of daily living, specific occupational tasks, and sports skills [57, 74]. Traditionally, these exercises are prescribed in sets and reps with long recovery periods and are said to have a minimal aerobic response [102]. But if performed in a high-intensity interval fashion, this modality can elicit aerobic and anaerobic adaptations as well as improve strength and power [102].

Cardiovascular fitness, muscular strength and endurance, neuromotor fitness, and cardiometabolic health are all components improved if one adheres to the published exercise recommendations (150 min/week-moderate aerobic training + 2–3 days/week-resistance training + daily flexibility training) [8, 22]. The time commitment to meet these recommendations is upwards of 250–300 min/week. For special populations, such as those with MetS, the recommendations increase the aerobic exercise to anywhere between 300 and 420 min/week [8]. If adherence to the general guidelines is poor due to the time commitment, a larger time commitment could likely increase that barrier. HIFT protocols seem to range between 20 and 40 min of exercise time, resulting in approximately 50–60 min per session if the warm-up, rest periods, and cool-down are included [57–63]. The HIFT interventions within the literature that demonstrated fitness and health improvements were performed 3–4 times per week, requiring a time commitment of 150–200 min, significantly less than the published recommendations [57–63]. However, it is unknown if health benefits are seen when HIFT is performed less than 3 times per week, therefore requiring even less time commitment. Thus, the exploration of this study.

Minimal dose, or minimal time commitment, exercise protocols are currently being explored aiming to combat the “lack of time” barrier to exercise [103, 104]. Most interventions modify modality, intensity, and/or load to therefore reduce duration and frequency, which ultimately reduces time commitment. For example, when aerobic intensity was increased to maximum, the duration of the session necessary for equivalent cardiorespiratory benefits was 67% less time than exercise at moderate intensity [105, 106]. Equivalent improvements in the markers of muscle lipid and carbohydrate oxidation were also found between the high-intensity and moderate-intensity groups [105]. The workload performed by the moderate-intensity group followed the general exercise guidelines of 150 min/week [8, 105], which are the same recommendations for blood lipid and insulin resistance improvements [107]. Although blood lipids and insulin resistance were not measured, it is possible these could be improved due to the mitochondrial remodeling seen, however with 67% less time commitment in the high-intensity group [105]. In another study investigating HIIT frequency, when high-intensity aerobic exercise (10 × 60s cycling at 83% peak power; ~ 20 min session) was performed only two times per week, significant improvements were seen in cardiorespiratory fitness and body composition [65].

Resistance training studies have also explored the minimal dose necessary for increases in strength and hypertrophy. To achieve gains, investigators have determined that resistance loads can vary (30–70% 1RM) as long as they are performed with high effort near volitional or momentary muscular failure [108]. When loads reached high amounts, the repetitions to failure were reduced, therefore reducing the time commitment [108]. These authors also determined that two of these training sessions per week was the minimum frequency to see increases in strength and hypertrophy [108]. In another dose-response study, sedentary adolescent males performed 1, 2, 3, 4, or 5 sets of a HIIT protocol (4 × 20s all-out exercise interspersed with 10-s rests), twice weekly plus one resistance training session per guidelines [8, 109]. Surprisingly, the group that performed 1 set (3 min 40s per week of HIIT) had equivalent decreases in visceral fat as the groups performing up to 5 sets (18 min 20 s per week of HIIT) [109]. Maximal oxygen uptake was improved in all groups with only a 1% greater improvement in the groups performing 4 and 5 sets [109]. These findings suggest that meaningful health benefits are gained with an extremely low dose of maximal HIIT twice weekly, plus one resistance training session [109]. All of these protocols require much less of a time commitment than the general guidelines state, yet still seem to provide beneficial metabolic and fitness adaptations.

To our knowledge, a minimal dose of exercise to see improvements in blood lipids, insulin resistance, and endothelial function has not been explored. In clinical practice, the current recommended exercise dose for blood lipid and insulin resistance is in line with the general recommendations, noting that higher volumes lead to further improvements [107]. Minimal dose hypotheses are worth testing, however, based on the demonstrated acute physiological responses, as insulin, glucose, and lipid changes have shown to last as long as 48 h after exercise [96, 110, 111]. The acute physiological responses to one session of exercise are the stimulus that leads to chronic adaptions when repeated and therefore should not be viewed in isolation [112].

Willis et al. quantified the intensity and energy expenditure of a typical HIFT workout in healthy men and women. During this 44-min exercise bout, the participant’s average HR was 80% of HR_max_ (range 69–100%), and the average energy expenditure was approximately 485 kcal (range 418–552 kcal) [63]. Although these authors did not measure any cardiometabolic markers, this has been acutely explored in other exercise interventions of the individual components of HIIT and resistance training. In healthy men performing an exhaustive cycling bout (~ 8 mins) at a high aerobic intensity of 93.5% ± 5% VO_2max_ yet lower energy expenditure (141 kcal ± 64.9 kcal) than a HIFT bout, saw significant decreases in TC and LDL-C immediate and 1-h post-exercise [113]. Also, in healthy men, when running intensity was lower (70% VO_2max_), immediate decreases in TC and LDL-C were not seen until an energy expenditure of 1300 kcal was reached, which took approximately 94 mins [114]. As the aerobic intensity and energy expenditure of a HIFT workout falls between the thresholds of these two studies, perhaps there is a sweet spot where beneficial acute blood lipid improvements can be seen. The research on acute blood lipid responses to resistance training is quite limited. One study exploring VLDL-TG kinetics the morning after evening exercise in untrained but healthy men, the authors found a 28% decrease in VLDL-TG concentration and a 30% increase in particle clearance rate after a 90 min resistance exercise bout expending ~ 400 kcal [115]. This demonstrates that resistance training has a potent acute effect on blood TG and could provide additional benefits when combined with acute lipid effects from high-intensity aerobic exercise, as is done in HIFT [8, 57].

Acute blood lipid responses seem to differ however in hypercholesterolemic (HC) men and women. Acute improvements in HDL-C and TG are commonly seen [95, 111, 116]. However, TC and LDL-C have shown an immediate decrease [95, 116], then return to baseline at 24 h [95] or rose above baseline at 24 h [116]. In another study of a 350-kcal cycling session at 80% VO_2max_, TC and LDL-C were elevated at 24 and 48 h after the session in HC men [96]. It is still unknown how hypercholesterolemic individuals may acutely respond to higher intensity intervals, as each of these studies explored steady-state exercise. “Exercise snacking” is a term to describe very short bouts of exercise (≤ 5 min) performed intermittently throughout the day and is often studied as a method to interrupt sedentary behavior [117]. The authors exploring this minimal dose approach found that 3 min of simple resistance like exercises (half-squat, calf raises, gluteal contractions, knee raises) performed every 30 min (total of 36 min/day) attenuated postprandial blood glucose, insulin, and triglyceride responses in type 2 diabetics [118].

The exercise-mediated improvements in cardiometabolic health are often not fully explained by the traditional risk factors of blood lipids, glucose, and insulin, but rather can be attributed to improvements in vascular health [45]. In untrained individuals with metabolic syndrome, one session of high-intensity aerobic training (4 × 4 min at 90–95% HR_max_ with 3 min rests between intervals) improved endothelial function from 5 to 11% immediately after, with a lasting effect for 72 h [119]. Perhaps the aerobic intensity, energy expenditure, combined modality, and time to completion of HIFT will be an ideal combination of factors to elicit acute lipid, glucose, insulin, and endothelial changes that could lead to chronic adaptations if performed frequently. The minimal dose of this repetition is unknown though. With the most commonly stated barrier to exercise as “lack of time,” minimal effective exercise dose investigations are highly warranted.

Not only is HIFT time-efficient, but HIFT is translatable to various physical settings. The equipment required is minimal, portable, and affordable compared to sophisticated cardio and resistance training machines found in most fitness facilities [57, 120]. Most HIFT protocols involve exercises with bodyweight, kettlebells, medicine balls, dumbbells, resistance bands, suspension bands, slam balls, stability balls, and other portable weighted equipment. The use of these types of “free weights” was concluded as #4 in the top 20 exercise trends of 2020 [56]. HIFT is popular [56], enjoyable [55], time-efficient [57], translatable to various settings [57], and elicits health and fitness benefits [57–63]. The results of this study will provide insight into the minimal dose of HIFT necessary for cardiometabolic health improvements in people with MetS. In turn, these findings will aid in the development of new exercise programming guidelines for MetS and related disorders.

